### Conceptual framework

The adapted Health Stigma and Discrimination framework [22] will guide several aspects of this work, including the development and implementation of the arts-based intervention. The framework provides a theory of HIV stigma processes by highlighting various domains of health-related stigmatization across the socio-ecological spectrum. We have adapted the framework to the local context through a consultation process with the District Education Officer and the District Health Officer. Adaptation includes applying the framework’s constructs related to the drivers of stigma and facilitators of prevention to minimize the harmful effects of stigma during data collection and analysis.

### Study support and oversight

#### Community Advisory Committee

A Community Advisory Committee (CAC) will advise the research team on the development, implementation, refinement, and evaluation of the arts-based intervention and participate in the interpretation and dissemination of findings. The 16-member CAC is comprised of research team members and locals holding various leadership roles (e.g., Village Health Team, education specialists), community members, and youth in rural villages in Omoro District. Though intermittently disrupted by COVID-19 containment measures, community engagement by the research team began on 05/2019 and is ongoing. The CAC will be engaged for in-person and virtual meetings (or as per COVID-19 protocols) and will meet a minimum of twice per year. All meetings will be audio recorded with the consent of the participants.

#### Trial Steering Committee

The Trial Steering Committee (TSC) will consist of the study’s Principal Investigator (BF) and Co-Investigators (JM, GM, OB), a Research Associate ([name]), a representative of the CAC, and an external Academic Advisor. The TSC will approve the final study protocol, coordinate with study stakeholders and the Study Support Team, and oversee all aspects of the trial, including implementation of the intervention in school settings. The TSC will also review trial data, report study results, and contribute to knowledge translation and dissemination. The committee will meet once per month.

#### Study Support Team

The Study Support Team (SST) will consist of Project Coordinators and Research Assistants located in Omoro District, Uganda. The SST will execute tasks required for recruitment, training, data collection, and monitoring /evaluation activities.

### Setting and participants

This study will take place in Omoro District, Northern Uganda, where the HIV prevalence among the 15–24 age group at 7.2% is 20% greater than the national prevalence of 6.0% [23]. Omoro District has a slightly higher pregnancy rate among young people of 28% among 10–18 year-olds compared to the national rate of 25%. HIV prevalence among young pregnant mothers who were tested at their first antenatal visit was 8.9% in the district compared to 7.6% for pregnant mothers nationally [23].

In Omoro District, there are seven secondary and 65 primary government-funded schools that serve six sub-counties (Koro, Lalogi, Odek, Bobi, Ongako, Lakwana, and Omoro). Each grade level enrolls approximately 50 students per school, with approximately 12,000 students enrolled across these grades. In this study, we will approach students ≥10 years of age in six grade levels for recruitment. Primary grades 5–7 include approximately *n*=150 students per school; secondary grades 1–3 include *n*=150 students per school. Therefore, we estimate *n*=1800 as the total number of eligible students attending 12 schools across eligible grade levels.

### Randomization

In consultation with the District Education Officer, we identified a sampling frame of all government-funded schools situated within Omoro District (65 primary and seven secondary schools). One secondary school (Awere Secondary School) and nine primary schools (Awere, Dino, Odek, Agweno, Jing Komi, Acet, Awali, Aromo Wanglobo, and Binya) were considered ineligible as travel time from the research office in Omoro District to the school was estimated to be 1 h or longer. From the eligible sampling frame of 56 primary and six secondary schools, one Co-Investigator independently used a random number generator in Stata 11.0 to randomly select (without replacement) and allocate six primary and six secondary schools to three crossover blocks. Other Investigators, members of the local research team, and Head Teachers did not have advance knowledge of the allocation prior to enrollment. After allocation to blocks, Head Teachers were invited to enroll their schools in the study. Three primary schools (Ajuri, Laminonami, and Kweyo) were resampled due to a land issue that closed the school, a bad road that blocked transit to the school, and an administrative redistricting that moved the school to neighboring Gulu District. All secondary schools agreed to participate. The research team will coordinate with Head Teachers to facilitate participation of all classrooms in each eligible grade level.

### Recruitment of students

Initial contact with students will occur after schools are randomized and enrolled in the study. The research team will read the information letter in Luo in the classroom before inviting students to participate. A copy of the information letter will be sent home with students for parents or guardians to review with a choice to opt out. We will return within the following week to obtain a list of students who are interested in participating. Verbal consent (≥10 years old with parental opt-out process) will be sought and documented in a tracking form. Students who decline to participate may join another classroom during study activities.

We will recruit three classrooms per primary school and three per secondary school (one classroom per grade level with one participating teacher per classroom). Elders will also participate in the intervention with one Elder assigned per classroom. Each Elder will participate in the intervention in three different classrooms per week. An Elder, as defined by CAC members, is a person who is knowledgeable in traditional and customary issues, a custodian of cultural knowledge, and presides over many societal issues on behalf of their community. Elders will be recruited through consultation with each Head Teacher.

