**Fig. 1 Fig1:**
[figure not shown]
SPIRIT flow diagram

The 32-week stepped-wedge cluster-randomized trial will be implemented in three blocks of four schools, each stratified by school type (primary, secondary), such that each block will consist of two schools of each type. The clusters are assembled into three blocks that will crossover from control to intervention condition, with crossover order selected at random. Including the control period, each school will participate across four 8-week periods with crossover from control to intervention condition occurring after each period [20, 21]. Clusters will receive the intervention over 24 weeks, 16 weeks, or 8 weeks depending on their block allocation (Fig. 2).

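### Block allocation is concealed only until each school enrolls, so student recruitment and the baseline survey can take place with the school's start date known

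*Protocol article*

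**What the plan says.** Under Randomization, one Co-Investigator selected six primary and six secondary schools and allocated them to three crossover blocks. Schools were approached next: "After allocation to blocks, Head Teachers were invited to enroll their schools in the study". The concealment statement reads "Other Investigators, members of the local research team, and Head Teachers did not have advance knowledge of the allocation prior to enrollment".

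Under Recruitment of students, student contact comes later still: "Initial contact with students will occur after schools are randomized and enrolled in the study". The research team does the inviting: "The research team will read the information letter in Luo in the classroom before inviting students to participate". Sign-up is voluntary and takes a second visit: "We will return within the following week to obtain a list of students who are interested in participating". Consent is individual: "Verbal consent (≥10 years old with parental opt-out process) will be sought and documented in a tracking form".

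Under Study design, the three blocks cross over "with crossover order selected at random", with 24, 16 or 8 weeks of intervention in a 32-week trial. Under Outcomes, the primary stigma measures are self-reported and are collected by independent research team members at baseline, every 8 weeks, and five months after the last block.

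**The concern.** In a cluster trial, concealment has to cover two decisions: the cluster's decision to join and the individual's. The protocol protects the first. For the second, it places every step (invitation, listing, consent, baseline answers) after the point at which concealment is last claimed.

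A student asked to join a programme that starts in 8 weeks is being offered something different from a student who would wait 24 weeks. Staff may also recruit harder where the start is near, and students may shade self-reported baseline answers if they know what is coming. The Discussion expects reluctance to take part because of HIV stigma, so there is a margin on which such differences could act. At stake is whether the three blocks contain comparable students, and so whether later differences between them can be read as intervention effect.

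**Working it through.** **1. Order of steps.** Allocation to blocks, then invitation and enrollment of schools (concealment last claimed here), then classroom approach, list of interested students, verbal consent, baseline survey, and finally crossover. The word enrollment in the concealment sentence refers to schools: the next sentence invites Head Teachers to enroll their schools, and the recruitment section speaks of schools being randomized and enrolled. No later section restores concealment. The assessors are called independent, but are not said to be unaware of allocation.

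**2. Start dates.** Trial length minus exposure: 32 − 24 = 8, 32 − 16 = 16, 32 − 8 = 24 weeks.

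**3. Room for selection.** Eligible: 12 × 150 = 1800. Expected in the final sample: 12 × 75 = 900. The other 900 combine refusal with later loss, because the 50% is stated after attrition. So 900 is an upper bound on non-participation at recruitment; the documents do not give the number who decline.

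**4. The plan's own figure.** This point does not change the power; reproducing it only checks the layout used in steps 5 and 6. The Hussey-Hughes variance is v = Iσ²(σ² + Tτ²) / [(IU − W)σ² + (U² + ITU − TW − IV)τ²]. Inputs from the Power calculation section: I = 12 schools, T = 4 periods, 75 students per school, ICC 0.01, 60% against 48%. I assume 75 students in each period.
- Design sums: U = 24, W = 224, V = 56, so IU − W = 64 and the second bracket is 160.
- With total variance 0.6 × 0.4 = 0.24: σ² = 0.24 × 0.99 / 75 = 0.003168 and τ² = 0.0024.
- v = 12 × 0.003168 × 0.012768 / (0.2028 + 0.3840) = 0.000827, so SE = 0.0288.
- Power = Φ(0.12 / 0.0288 − 1.96) = 98.7%. With variance 0.54 × 0.46 it is 98.4%. The protocol states 98%.

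**5. What block fixed effects remove.** Assume selective joining makes true prevalence 5 points lower in the early block and 5 points higher in the late block throughout. Generalized least squares on this layout, with period effects and ICC 0.01, gives:

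| Model | Within-student correlation 0 | Within-student correlation 0.5 |
|---|---|---|
| No block effects | −2.6 points | −1.0 point |
| Block fixed effects, as planned | 0 | 0 |

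The shifts are assumptions. The zero is exact for any constant shift, because the block terms absorb it.

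**6. What they leave.** With block and period effects, the estimate weights each block-by-period mean by the doubly centred treatment indicator. In twelfths, over periods 1 to 4:
- first block: −3, 5, 1, −3
- second block: 0, −4, 4, 0
- third block: 3, −1, −5, 3

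The sum of squares is (44 + 32 + 44)/144 = 5/6. From these weights:
- *Dropout or drift:* a change of d in the third block in periods 2 to 4 only shifts the estimate by [(−1 − 5 + 3)/12] d ÷ (5/6) = −0.3d. If d is 5 points, that is −1.5 points.
- *Trend:* an extra linear change of h per period in the first block alone shifts it by [(5 + 2 − 9)/12] h ÷ (5/6) = −0.2h. The third block's coefficient is also −0.2, so equal and opposite linear trends in these two blocks cancel.
- *Response:* if the true effect differs by block, the estimate is 0.3, 0.4 and 0.3 times the three block effects, so it depends on who joined which block.

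These examples use a single step effect and categorical periods, which is simpler than the planned time terms. They show that block effects are not full protection, but do not estimate the actual bias.

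**The case against.** The strongest reply is that the article never says the order is announced. A reader might infer from the sequence that recruiters and students do know their start date. The documents do not support that: they let concealment lapse at school enrollment and are silent afterwards. When each party learns the date is a detail a full protocol could hold. This stands, so the point is that knowledge is possible and unguarded, not that it is established.

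A reader might also infer that school staff select the students. Recruitment of students gives the invitation to the research team; Head Teachers only help arrange classroom participation. Nor can the 900 students outside the final sample be read as 900 open to selection by start date: the Discussion ties attrition to COVID-19 absence and pregnancy, and ties reluctance to stigma rather than timing.

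The design has real safeguards too. The approach is classroom-wide with a read-out letter and parental opt-out, assessors are independent, every school has its own control period, and block fixed effects are planned. These reduce the concern. None of them keeps the start date from those who recruit, consent or answer at baseline.

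**Conclusion.** The point holds as an inexpensive improvement, not as a demonstrated bias. The stated concealment covers the school's decision to join and stops before students are approached, consented and surveyed. Constant differences in level between blocks are removed by the planned model. Differences in trend, response or dropout between those who joined are not removed in general.

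The size cannot be derived from the documents. The −1.0 to −2.6 points without block effects and the −1.5 points with them, against a planned difference of 12 points, rest on assumed 5-point shifts. The conclusion assumes that enrollment in the concealment sentence means the school's, and that no unpublished text extends concealment to student recruitment. The 98% power is unaffected.

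**What to change.** Amend Randomization and Recruitment of students to state that the existing block order stays with the allocating Co-Investigator. It is not released to recruiters, baseline assessors, Head Teachers, teachers or students until consent lists and the baseline survey are complete in all 12 schools. Until then they know only that the start will be at week 8, 16 or 24. Report the numbers approached, consenting and surveyed at baseline by block.

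No redraw is needed if the order has not yet been disclosed. If some of it has, state to whom and when.

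This is feasible on the article's own account. Student recruitment had not begun at version 2.0, training is one common workshop, and all schools are in the control condition for the first 8 weeks. The cost is shorter notice of the start date: about 8 weeks for the first block, provided baseline is finished by week 0, which the article does not state. Dropout caused by a longer wait would remain, so the planned attrition sensitivity analyses are still needed.

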### Arts-based HIV stigma reduction intervention

#### Formative research phase

For pilot-testing, we will conduct six formative semi-structured interviews in Luo with one student and one teacher recruited by Head Teachers at one primary and secondary school, and two Elders. We will conduct an additional 50 one-on-one formative semi-structured interviews lasting 30–60 min, with purposively selected eligible students, Elders, and teachers at participating schools.

The initial interview guide will be created by the research team and revised with feedback from pilot interviews and the CAC to ensure cultural and contextual relevance. The interview guide will be drafted in English and translated to Luo. The guide will include questions for students, teachers, and Elders, such as “How are people who are known to be HIV-positive treated in your community, family, or school?” and “How does your village treat HIV-positive persons?” Data from the full set of formative qualitative interviews will be used to inform modifications to quantitative survey instruments.

In coordination with Head Teachers, 24 students aged ≥10 years, balanced by gender, and attending a participating primary or secondary school in grades primary 5–7 or secondary 1–3 will be invited to participate in one-on-one formative interviews. Additionally, 16 teachers will be recruited by the Head Teacher. Elders in the community will be identified based on competence in local language and demonstrated skills and practices in intergenerational knowledge transfer. Approximately five Elder women and five Elder men will be recruited through the Waroco Kwo Elders Association. The research team will attend an Elders’ meeting to facilitate discussions about the study and provide copies of the information letter/consent form. Interested Elders will contact the study’s research officer. Verbal informed consent will be obtained through information letters/consent forms translated and read to participants in Luo. Verbal consent from parents/guardians will be obtained for students. Participants will have the choice to opt out at any time.

#### Workshops

Following the formative research phase, one 3-day intervention training workshop will be delivered in collaboration with Elders, CAC members, teachers, and Head Teachers from participating schools. Workshops will serve to establish relationships between teachers and Elders, review findings of the formative phase, provide research ethics training, review the HIV-related stigma curriculum, and deliver several of the HIV stigma educational activities to practice facilitation of classroom discussions. The workshops will build the capacity for teachers and Elders to facilitate the intervention sessions with participating students in their classrooms.

#### Intervention components

The intervention will be delivered 2 h per week over 24 weeks and will consist of three interrelated activities: (1) transformative educational activities, (2) arts-based activities, and (3) participatory theater. These activities will address the drivers of HIV-related stigma (i.e., fear and misconceptions about HIV, lack of awareness, social judgment, shaming, prejudice, negative attitudes and reluctance to seek treatment or help), which manifest as types of stigma practices (i.e., enacted, internalized, anticipated, courtesy, perceived) [22].

Students will be eligible to participate in the arts-based intervention if they are ≥10 years of age, live in Omoro District in northern Uganda, attend a government-funded primary and/or secondary school in Omoro District during the study period, and are enrolled in primary grades 5–7 or secondary grades 1–3.

##### Transformative educational activities

Transformational educational activities will be based on Dewey’s [24] educational approach by grounding in the daily experiences of young people where stigmatizing experiences and practices are manifest. In the first hour of the weekly session, transformative educational activities will engage learners in problem-based discussions initiated with pictures from an HIV stigma toolkit that was created, implemented, and evaluated in sub-Saharan Africa with youth and adults [25]. The toolkit addresses drivers, facilitators, and manifestations of stigma as a means of articulating a “problem.” Learning through practice (i.e., participatory learning) will be emphasized through role play, discussion, and issue analysis.

##### Arts-based activities

These activities are anchored in aesthetics, i.e., theory of artful expression [26], and influenced by Eisner’s view that arts-informed research entertains, educates, and acknowledges individuals as knowledge-makers [27]. A key advantage of using art is to access “ways to perceive and interpret the world…that would otherwise go unknown” [27].

During the second hour of the weekly session, the focus will shift to addressing the “problem” through finding “solutions” and encouraging action by learning traditional Ugandan songs and dance; told and acted stories; proverbs and sayings that incorporate empowering messages and moral teachings connected with respect for the relationship between oneself and the community, peers and Elders; and responsibility for others. By grounding the intervention in local culture, this knowledge will reinforce the transformational learning needed to address the root causes of HIV stigma (e.g., stigma toward sex and adolescent sexual and reproductive health) while directly addressing each stigma type (i.e., enacted, internalized, anticipated, courtesy, and perceived). Drawing on the work of Paulo Freire, problem-based identification and discussion occurring in the first hour will be connected with development of problem-solving skills in the second hour [28]. Students will also be invited to write stories and music lyrics or create visual art that draws on their experiences with HIV-related stigma. The audio recordings of weekly sharing sessions will generate data for the process evaluation. Filming of storytelling sessions with Elders during the intervention will serve as knowledge preservation activities that promote intergenerational inclusion.

##### Participatory theater

After five weeks of intervention activies, a participatory theater intervention (PTI) will occur over the following 3-week period. Developed in collaboration with students, the PTI will summarize learning and cultural traditions from previous sessions. The first week will be dedicated to developing the forum theater event. The remaining two weeks will be dedicated to performances in front of audiences, including students, parents, and community members. Five topical scenes will be developed per school in collaboration with theater specialists, researchers, students, Elders, and teachers. Scenes will be developed through performance techniques [28] that will include a summary of qualitative data findings from formative interviews. Each scene will incorporate examples of stigma types (i.e., enacted, internalized, anticipated, courtesy, and perceived) with an HIV-positive and HIV-affected participant (student actor) who will perform each stigma domain. For example, student actors will portray a student who is living with HIV and experiencing internalized stigma and anticipated stigma; a student not living with HIV who is enacting stigma; a student who is experiencing courtesy stigma because of a mother living with HIV; and a student who perceives stigma in their community. Additionally, after enacted situations that present a problem with no solution, an audience member will be invited to enact a positive solution.

A semi-structured focused discussion will be held immediately after the PTI to explore participant and audience experiences. These discussions will be recorded and transcribed, providing qualitative data for the process evaluation.

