### Outcomes

Outcomes will include self-reported stigma-related measures and clinical measures. The primary outcomes are enacted, anticipated, and internalized stigma as measured using the *Adolescents Living with HIV—Stigma Scale* [30]. Secondary outcomes will include courtesy and perceived stigma measured using *Stewart et al.’s 10-item subscale* [31] and the *Brief Stigma by Association Scale* [32]. Secondary clinical outcomes will include HIV testing frequency among sexually active participants; and linkage to care, time to initiation of antiretroviral therapy (ART), ART adherence, and viral suppression, among participants living with HIV. Study outcomes will be assessed by independent research team members at baseline, following each crossover period (i.e., every 8 weeks), and 5-months after completion of the final intervention block.

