### Power calculation

Using the power and detectable-difference calculations for stepped-wedge cluster-randomized trials (91) (Stata 14.2), we calculated 98% power to detect a 20% reduction (i.e., an absolute risk difference of 12%) in the proportion of young people reporting a stigma endpoint (i.e., endorsing sufficient elements in the primary stigma measure) given a baseline proportion of 60% experiencing HIV-related stigma, a 5% two-tailed type I error rate, and an intra-cluster correlation coefficient (ICC) of 0.01. There is a lack of published ICC estimates in this setting. Prior work in sub-Saharan Africa and rural Uganda found that 50% of participants experienced stigma in some form [33]. Given our team’s prior experience working among young people in areas recovering from conflict, we have assumed a higher baseline proportion of 60% to have experienced HIV-related stigma. We targeted a total cluster size of 12, with four schools (two primary and two secondary) grouped to crossover from control to intervention at three specified crossover points. We estimate that there will be 150 students enrolled per school across eligible grade levels. Assuming a 50% participation rate after attrition, we estimate that the evaluation will reach 75 students per school for a total sample of *n*=900 who will complete the surveys at the end of the final data collection period﻿ [34].

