### Data collection and management

#### Survey design and measurements

A survey questionnaire will assess primary and secondary outcomes, along with selected covariates. The questionnaire will be developed in English and translated into Luo. The questionnaire will be refined with input from the CAC and pretested with 6–10 students to evaluate ease of comprehension, suitability of questions, and completion issues. Internal consistency of relevance scales (e.g., attitudes, stigma) will be assessed using Cronbach’s alpha.

The questionnaire will take up to 60 min to complete and will include questions about socio-demographics, reproductive and sexual health behavior, HIV testing, and HIV care. Stigma outcomes will be measured using three validated scales:Enacted, anticipated, and internalized stigma among HIV-positive students will be measured using the *Adolescents Living with HIV—Stigma Scale* [30].Courtesy stigma will be measured using the *Brief Stigma by Association Scale in HIV-affected students* [31].Perceived stigma will be measured using *Stewart’s 10-item subscale on felt-normative stigma towards PLHIV* in their community [32].

As intervention benefits may attenuate over time [35], we will examine sustainability of attitudinal change and stigma-associated change five months after the intervention has ended. Sexual risk, HIV testing frequency, and HIV status will be assessed by self-report.

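### Theater performances with community audiences fall just before the only two surveys that have concurrent control schools, and the protocol describes no measure of control students' exposure to them

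*Protocol article*

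**What the plan says.** All references are to the protocol article.

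- **Participatory theater** sets the timing: "After five weeks of intervention activies, a participatory theater intervention (PTI) will occur over the following 3-week period". The first of the three weeks is for development. Of the rest it says: "The remaining two weeks will be dedicated to performances in front of audiences, including students, parents, and community members".
- **Study design** fixes the calendar: "each school will participate across four 8-week periods with crossover from control to intervention condition occurring after each period", and "Clusters will receive the intervention over 24 weeks, 16 weeks, or 8 weeks depending on their block allocation".
- **Outcomes** fixes the surveys: "Study outcomes will be assessed by independent research team members at baseline, following each crossover period (i.e., every 8 weeks"), with a further assessment five months after the last block finishes.
- **Power calculation** has "four schools (two primary and two secondary) grouped to crossover from control to intervention at three specified crossover points".
- **Randomization** draws the schools from one district: "From the eligible sampling frame of 56 primary and six secondary schools", of which six primary and all six secondary schools are in the trial.
- **Survey design and measurements** assesses perceived stigma with a "10-item subscale on felt-normative stigma towards PLHIV" in the student's own community.

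Process evaluation names reach and context among its components, and discussions held after the performances are recorded as qualitative data. Neither these sections nor Analysis of survey data describes a measure of, or a model term for, attendance by students whose school is still a control.

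**The concern.** The performances are an active part of the intervention and reach beyond the performing school. They end exactly when the next survey is due. If students of control schools, or people in their households, attend, part of the effect reaches the comparison group shortly before its outcome is measured. That would pull the estimated effect toward zero. Perceived stigma is the outcome most open to this, because it asks about the community that the performances address.

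If attendance is not recorded at the time, a small estimated effect could mean a weak intervention or an exposed control group, and the trial could not tell which. Attendance cannot be reliably reconstructed later.

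**Working it through.** **1. Timetable.** Five weeks of activities plus three of theater make 8 weeks, so performances fall in intervention weeks 7-8.

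| Block | Intervention starts after week | First performances | Next survey | Control schools at that survey |
|---|---|---|---|---|
| 1 | 8 | 8+7 to 8+8 = weeks 15-16 | 16 | 8 (blocks 2, 3) |
| 2 | 16 | 16+7 to 16+8 = weeks 23-24 | 24 | 4 (block 3) |
| 3 | 24 | 24+7 to 24+8 = weeks 31-32 | 32 | 0 |

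At weeks 0 and 8 every school is a control; at week 32 none is. So all 8 + 4 = 12 concurrent control school-surveys directly follow performances. This holds whether theater happens once per block or in every 8-week cycle.

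**2. The plan's own power figure.** Inputs from Power calculation: 60% against 48%, two-sided 5%, ICC 0.01, N = 12 schools, 75 students per school. I take T = 4 periods, with 75 students surveyed in each. The Hussey-Hughes variance is

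Var = N s² (s² + T t²) / [(NU - W) s² + (U² + NTU - TW - NV) t²]

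- Mean proportion 0.54, so total variance is 0.54 × 0.46 = 0.2484.
- s² = 0.99 × 0.2484 / 75 = 0.003279; t² = 0.01 × 0.2484 = 0.002484.
- U = 24 intervention school-periods. W = 0² + 4² + 8² + 12² = 224. V = 4 × (3² + 2² + 1²) = 56.
- Numerator: 12 × 0.003279 × (0.003279 + 4 × 0.002484) = 0.000520.
- Denominator: 64 × 0.003279 + 160 × 0.002484 = 0.6073.
- SE = √(0.000520 / 0.6073) = 0.0293.
- Power = Φ(0.12 / 0.0293 - 1.96) = 98.4%, which reproduces the stated 98%.

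**3. Attenuation if every control school is affected.** Let X = 1 for an intervention school-period, θ the true effect, and c the share of it that reaches control schools at weeks 16 and 24. In every wave after the first crossover the expected shift is

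θX + cθ(1 - X) = cθ + (1 - c)θX

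The constant cθ goes into the period effect, which leaves (1 - c)θ as the estimate. Generalized least squares with a random school effect gives a coefficient of exactly -1.000 per unit of c. Linear trial time in place of period terms gives the same. The clean data at weeks 0 and 8 do not offset it.

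**4. Attenuation if only secondary schools are affected.** Each block has two primary and two secondary schools, so half of the control school-surveys are secondary. The coefficient is then -0.500, and the estimate is (1 - c/2)θ.

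| Assumed c | All control schools | Power | Secondary only | Power |
|---|---|---|---|---|
| 0 | 12.0 points | 98% | 12.0 points | 98% |
| 10% | 10.8 points | 96% | 11.4 points | 97% |
| 25% | 9.0 points | 87% | 10.5 points | about 95% |

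The documents give no spillover figure, so every value of c is an assumption.

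**The case against.** A reader might infer that the performances are open to anyone and that control students will attend. The text supports neither. It names community members among the audience, but gives no admission rule or venue, no distances between schools, and no instance of a control student attending.

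The geographic argument is also only half as strong as it looks. It rests on the trial taking all six eligible secondary schools, whereas the primary schools are six of 56 eligible.

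A large c is hard to credit. By its first survey an intervention school has had about 2 h × 8 weeks = 16 hours and has built the theater itself. A control student could at most have watched some performances, and c averages over all control students, including those who saw nothing. At c=10% the power loss is immaterial. The points and power above also refer to the primary stigma endpoint, while the clearest route to spillover concerns a secondary outcome.

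Finally, attendance logs and sensitivity analyses often sit in a manual or full protocol, and the process evaluation does name reach and context.

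Most of this stands, and it limits the size of the point. What it does not remove is the timetable, which the article itself fixes. The process-evaluation methods it describes (classroom observation, brief discussions, interviews, recorded discussions) would not yield a dated exposure measure for control school-periods.

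**Conclusion.** The point holds as a possible, unmeasured spillover. Performances with community audiences directly precede all 12 concurrent control school-surveys, and nothing in the text keeps control-school students away or records whether they came. Any effect would probably be dilution toward the null, chiefly for perceived stigma. At an assumed c between 10% and 25%, the estimate would be 10.8 to 9.0 points if all control schools were affected, or 11.4 to 10.5 if only secondary schools were. These figures assume a constant intervention effect and the same c at both surveys.

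A reader might go further and conclude that the control group is contaminated or the trial underpowered. The documents support neither: no spillover is shown, its size is unknown, and the 98% power reproduces on its stated inputs. This is a cheap improvement to make before the first performances, not a flaw that invalidates the design.

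**What to change.** 1. Keep the community performances as planned. In Participatory theater, add that students of trial schools still in the control condition are not invited to performances at other schools before the week-24 survey is complete.
2. Add one dated item to each 8-week survey: has the student, or anyone in the household, attended a study performance at any school?
3. Pre-state a sensitivity analysis that codes control school-periods by the proportion so exposed.

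Cost: one sentence of protocol text, one survey item and one extra analysis. The exclusion cannot be fully enforced, which is why the survey item matters. The exposure-coded analysis is not protected by randomization and rests on 12 control school-surveys, so it can only support the main result.

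Closing the performances to community members until after week 24 would limit exposure more tightly. I do not recommend it, because it would remove a stated intervention component from blocks 1 and 2 at the two waves that supply the concurrent contrast.
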